The patients’ testimonies show that the first reaction during an AAGA is usually to move to alert the medical staff [2,17]. Unfortunately, during most surgeries, the patient is curarized, which causes neuromuscular block and prevents any movement. Detecting movement intention (MI) is possible by analyzing EEG signals from the motor cortex with a brain-computer interface (BCI). This is based on previous evidence demonstrating that simple MIs are characterized by power spectrum variations (ie, event-related (de)-synchronization called ERD/ERS) in the EEG mu (7-13 Hz) and beta (15-35 Hz) bands over the motor cortex [18] and that electrical stimulation of the median nerve also induces changes in the cortical activity [19,20], which are visible in the EEG signal and which are similar to an MI [21,22]. Interestingly, our preliminary results suggested that when a hand MI coincides with median nerve stimulation (MNS), the ERD/ERS is considerably reduced, and thus the MI can be detected much better by machine learning techniques than an MI without MNS [23-26]. The originality of this BCI paradigm is to exploit this MNS-induced phenomenon to accurately detect the patient’s motor intention during an AAGA. Based on these previous results, we envisage a routine procedure where the anesthetized patient is stimulated by electrical pulses delivered at the median nerve position at the wrist, while a BCI device analyzes the ERD and ERS modulations over the motor cortex to detect the intention of movement of the patient. Our previous clinical trial (MOTANA protocol [23]) also includes a condition with MNS and another with MNS accompanied by MI for 3 concentrations of propofol (0, 0.5 µg/mL, and 1 µg/mL). The preliminary results (n=15) highlighted the advantage of a BCI based on MNS from both a functional and an accuracy point of view. First, MNS intrinsically provides a trigger to know when to analyze the signal. Second, the classification accuracy of an MNS-based BCI appeared to be way better than that of a BCI aiming to discriminate a motor imagination from a resting state. More precisely, an MNS-based BCI detected the MI state 15% more accurately. For several subjects, the use of MNS improves performance by more than 20% compared to a standard method [22,25].

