### EEG Data Acquisition

Motor EEG signals will be collected through the OpenViBE software platform with eego mylab system (ANT neuro) 64-EEG channels, covering the entire scalp at 16,000 Hz and 1 external channel placed on the dorsum of the contralateral hand to the electric stimulation, by means of an adhesive surface electrode. All offline analyses will be performed using the EEGLAB toolbox [34] and Matlab2016a (The MathWorks Inc). The findings will be additionally investigated by applying a Laplacian filter and a mastoidal re-referencing [35]. Then, the EEG signals will be resampled (128 Hz) and epoched into 6-s windows (1 second before and 5 seconds after the MNS). We will compute the ERD/ERS% using the “band power method” [36]. Additionally, SEP will be calculated by averaging epochs extracted from 0.25 to 0.5 with respect to the electric shock.

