### Statistics

The data processing methods will be similar to those described in the MOTANA protocol [23]. For each patient and each MNS, the maximal value of ERD and ERS max will be, respectively, selected in (0.25;0.5) seconds and (2;4) seconds after stimulation, in accordance with the literature [24,37]. An average over the ERDs max and ERSs max will be performed for each concentration. These 2 values will be, respectively, compared with average ERDs max and ERSs max obtained in the preoperative rest condition with a Student *t* test (*P*<.05). To visualize the event-related spectral perturbations with the EEGLAB toolbox, a surrogate permutation test will be used (*P*<.05; 2000 permutations). In addition to the permutation test, we will apply a false discovery rate correction to show the difference in MNS effect during different concentrations of propofol.

In addition to the event-related spectral perturbation analyses, we will apply 4 different offline machine learning algorithms to detect the MNS at the cerebral level. To do this, these algorithms are based on 4 classification methods in a 4-fold cross-validation scheme. The classification score will be computed for the MNS versus the rest class. Each trial will be segmented into a motor task time window and a resting time window, both lasting 2 seconds. The motor task time window will begin 0.5 seconds after the MNS, and the resting phase time window will begin 3 seconds before the MNS. The first classification method is a linear discriminant analysis method using a common spatial pattern [38] (referred to as common spatial pattern+linear discriminant analysis). For the next 3 classifiers, we will use classifiers that are based on Riemannian geometry. Riemannian geometry-based methods have the advantage of being immune to linear transformations and to be particularly efficient for the detection of motor intentions. For the statistical differences in the latency and topographic voltage of the SEP components, similar permutation tests and post hoc tests will be applied.

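### With 2000 permutations, a false discovery rate correction over a whole time-frequency map can declare nothing until about 1% of the map is rejected, which can hide sparse differences between propofol concentrations

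*Protocol article*

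**What the plan says.** The Statistics section introduces the test by its purpose, "To visualize the event-related spectral perturbations with the EEGLAB toolbox", and says that "a surrogate permutation test will be used" at P<.05 with "2000 permutations". The next sentence adds the correction aimed at the concentrations: "In addition to the permutation test, we will apply a false discovery rate correction to show the difference in MNS effect during different concentrations". The procedure, its level, the family of tests and the p-value convention are not given.

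Other places set the scale of the map:

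- EEG Data Acquisition has 64 channels, resampling to 128 Hz, and signals "epoched into 6-s windows (1 second before and 5 seconds after the MNS").
- Statistics takes the maximal ERD and ERS, respectively, "selected in (0.25;0.5) seconds and (2;4) seconds after stimulation".
- The Introduction places the modulations "in the EEG mu (7-13 Hz) and beta (15-35 Hz) bands over the motor cortex".

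The primary end point is ERD amplitude, tested by a paired Student t test (Primary End Points).

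**The concern.** A permutation p-value cannot be smaller than the number of permutations allows, whereas a false discovery rate correction over many cells asks for very small p-values unless many cells are rejected together. If the two settings do not fit, an empty map has two possible meanings: the concentrations do not differ, or the p-values were too coarse to show that they do.

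This matters for the secondary objective, which is how ERD and ERS change with each propofol concentration. The Discussion concedes that ERD/ERS may disappear at deep levels of anesthesia. A contrast between two deep levels may therefore be sparse or null, which is where coarse p-values do harm.

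**Working it through.** The article states no derived figure to reproduce, so the check starts from its settings.

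**Inputs from the article.** B = 2000 permutations; 6-s epoch; search windows of 0.25 s (ERD) and 2 s (ERS); mu 7-13 Hz (6 Hz wide); beta 15-35 Hz (20 Hz wide); 64 channels; 128 Hz.

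**Assumptions.** Benjamini-Hochberg at q = 0.05; a frequency axis between 7-35 Hz (28 Hz wide) and 1-64 Hz (63 Hz wide); cells evenly spaced in time and frequency; search windows used as a stand-in for the extent of an effect.

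**Step 1: the limit.** The smallest p-value is p_min = 1/(B+1) = 1/2001 = 0.00050. The step-up rule rejects k of m cells only if the k-th smallest p-value is at most kq/m, so it needs k/m ≥ p_min/q.

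- One-sided, or on an absolute statistic: 0.00050/0.05 = 1.0% of the family.
- Tails doubled: (2/2001)/0.05 = 2.0%.
- A single cell can be declared if m ≤ 100 (50 if doubled). One 6-s row at 128 Hz already has 6 × 128 = 768 samples, so a whole map would normally exceed this.

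**Step 2: share of the map an effect could occupy.**

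| Difference present | Formula | Share |
|---|---|---|
| Mu ERD, one channel | (0.25/6) × (6/63 to 6/28) | 0.4-0.9% |
| Mu-plus-beta ERD, one channel | (0.25/6) × (26/63 to 26/28) | 1.7-3.9% |
| Beta ERS, one channel | (2/6) × (20/63 to 20/28) | 10.6-23.8% |
| Mu-plus-beta ERD at 2-6 of 64 pooled channels | 1.7-3.9% × (2/64 to 6/64) | 0.05-0.36% |
| Beta ERS at 2-6 of 64 pooled channels | 10.6-23.8% × (2/64 to 6/64) | 0.33-2.2% |

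Against the 1% limit, a mu-only ERD on one channel and an ERD alone on a pooled map fall short. Mu-plus-beta ERD and ERS on one channel clear it. Pooled ERS lies on both sides. Against the 2% limit, mu-plus-beta ERD on one channel also lies on both sides.

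**Step 3: the limit applies to the family total.** In a simulation of 5000 independent cells (300 runs), with every effect cell at the smallest p-value:

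- An effect in 0.2% or 0.5% of cells, alone, was never declared.
- An effect in 1.05% of cells was always declared.
- An effect in 0.3% of cells, beside another in 5%, was declared in every run.

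**Step 4: if zero p-values are allowed (p = b/B).** A null cell exceeds all 2000 permutations with probability 1/2001, and p = 0 passes any correction. For m independent null cells the chance of at least one false point is 1 − (2000/2001)^m: 4.9% for m = 100, 39% for 1000 and 92% for 5000. The same simulation compared false discovery rates with the 5% target:

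| Effect share | p = b/B | p = (b+1)/(B+1) |
|---|---|---|
| 0 | 0.91 | 0.00 |
| 0.2% | 0.19 | 0.00 |
| 0.5% | 0.09 | 0.00 |
| 2% | 0.068 | 0.046 |
| 5% | 0.055 | 0.045 |
| 20% | 0.040 | 0.039 |

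**The case against.** The strongest reply is that the article does not give the premises. Procedure, level, family, pooling over channels and p-value convention are all unstated, and a journal article may leave them to a fuller document. In a family of up to 100 tests, for instance one test per channel, 2000 permutations suffice for a one-sided test. This stands, and it makes the point conditional.

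A reader might infer that 2000 permutations are simply too few, or that any effect covering less than 1% of the map is invisible. The documents do not support that: the limit is on all rejections together, and a small effect beside a large one can be declared (step 3).

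A reader might also infer that the primary ERD always lies below the limit. It does not. The Introduction places ERD/ERS in both bands, and mu-plus-beta ERD is above 1% of a single-channel map. Moreover, the 0.25-0.5 s interval is where a maximum is searched for. Nothing says that the desynchronization ends there, so the shares in step 2 are indicative only.

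Nothing indicates that zero p-values will be used. Neighbouring cells are also correlated, so the independent-cell figures in step 4 overstate how often a null map shows a false point.

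Finally, the permutation test is introduced for visualization. The t tests of ERD and ERS at each concentration against the preoperative condition do not depend on it. That limits the consequence, but the correction is still the stated way to show differences between concentrations.

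**Conclusion.** The concern holds in a conditional and minor form. Given a step-up correction at 5% over a whole time-frequency map, 2000 permutations mean that nothing is declared until total rejections reach about 1% of the family (2% if tails are doubled). This can bind for sparse contrasts, such as a mu-only ERD difference on one channel (0.4-0.9%) or an ERD difference without an ERS difference on a map pooled over 64 channels (0.05-0.36%). It does not bind on a single-channel map with the one-sided limit when ERS or mu-plus-beta ERD also differs.

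Loss of error control arises only if zero p-values are allowed and effects are absent or sparse; (b+1)/(B+1) prevents it. The primary paired t test on ERD amplitude is untouched. The conclusion rests on the assumed procedure, level, family and frequency axis, and on the search windows as a proxy for the extent of the effect.

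**What to change.** Compute p = (b+1)/(B+1), raise the number to about 20,000 permutations, and limit the family to prespecified sensorimotor electrodes and the 7-13 and 15-35 Hz bands. The limit becomes (1/20,001)/0.05 = 0.10% of the family (0.20% if tails are doubled).

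Both parts are needed. Restricting the bands alone puts a single-channel mu ERD at (0.25/6) × (6/26) = 0.96%, still just under the 1.0% limit at 2000. More permutations alone leave a pooled 64-channel ERD (0.05-0.36%) on both sides of 0.10%.

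Alternatively, keep 2000 permutations and replace the pointwise correction by a cluster or maximum-statistic permutation test. Each map or cluster is then judged directly against 0.05, where the Monte Carlo standard error is √(0.05 × 0.95/2000) = 0.005.

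The first option costs computing time and a sentence of wording. The second gives cluster-level rather than point-level inference if clusters are used. Neither changes the primary analysis.

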### Study Duration

The duration of the participation is from 45 minutes before surgery (installation of the EEG cam and the median nerve stimulator) until the end of surgery.

The expected overall duration of the research, including the time required for the completion of the data analysis, is 4 years. The promoter (CHU Brugmann) reserves the right to stop the research (1) if serious, there are significant procedural deviations in the protocol that could impact the statistical analysis of the data, (2) if recruitment of subjects is not adequate, or (3) if a significant issue regarding the safety and rights of the subjects arises.

### Data Collection

Data will be collected with a case report form and patient data will be anonymized (ie, a unique study number will be assigned to each individual). The case report form will contain demographic information of the patient, undesirable events which may be experienced during the study, the anesthesia chart will be photocopied at the end of the procedure and anonymized, and EEG data stored electronically under the supervision of the principal investigator.

### Patient and Public Involvement

A total of 30 patients will be involved in the STIM-MOTANA protocol. Patients, patient advisors, and the public were not involved in the development of the research questions or in the design of the study. Patient involvement in the study includes answering survey questionnaires at baseline and at each follow-up. Summaries of study results will be disseminated to study participants via email or mail. The results will be published in international peer-reviewed journals, and summaries will be provided to the funders and patients.

## Results

### Evaluation Criteria

#### Primary End Points

A total of 30 patients will be involved in the STIM-MOTANA protocol. We will compute the amplitude of ERD/ERS modulations before and after each MNS during the different phases of anesthesia at 2 different times: when the patient is awake before surgery and under general anesthesia. The primary evaluation end point will be the amplitude of the ERD. According to the Pfurtscheller method, ERD/ERS modulations will be calculated using a baseline taken before each stimulation [36]. The changes in ERD/ERS during MNS according to the various propofol concentrations will be continuously monitored. To compare the motor EEG signal before and after injection of the anesthetic product, we will apply paired statistical tests (Student *t* test).

#### Secondary End Points

In this project, we need to reach the highest MI EEG detection accuracies as possible, which is necessary in the context of a surgery for which we need a very high true positive rate (ideally all AAGAs are detected) as well as a very low false positive rate (ideally no false alarm). To do so, we will build BCI classifiers based on Riemannian geometry [22,24] a framework in which EEG signals are represented as covariance matrices, which are directly analyzed and classified.

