## Discussion

### Principal Findings

STIM-MOTANA is an interventional study aimed at designing an innovative BCI-based EEG-motor brain activity, which would detect the intention to move of a patient during general anesthesia. STIM-MOTANA is the first study to investigate cerebral motor activity modulations following peripheral nerve stimulation during general anesthesia.

AAGA can occur unexpectedly and is therefore a complication that cannot be easily anticipated and that is only retrospectively diagnosed. The STIM-MOTANA protocol proposes to detect intraoperative awareness reliably by analyzing, in real-time, brain motor activity under general anesthesia with a BCI based on MNS and new machine learning methods. Designing such a BCI presents us with 2 challenges. The first one is to detect the MI of a person who is a victim of AAGA without any time marker presented to the subject (ie, asynchronously) since, during AAGA, it is impossible to ask and know exactly when the patient will intend to move. Unfortunately, the literature clearly shows insufficient classification accuracies and high false positive rates with asynchronous BCI [22]. The second challenge is, therefore, to obtain a high level of accuracy (>90%—the minimum required accuracy according to the clinical application) to ensure a reliable BCI device that can be used in hospitals. To satisfy these 2 requirements, our objective is to design a robust MNS-based BCI. Based on strong practical and theoretical scientific reasoning from our previous studies, our innovative MNS-based BCI would provide a way to detect intraoperative awareness during general anesthesia. The primary limitation of this study is that ERD/ERS habitually generated by media nerve stimulation without anesthetic may disappear for deep levels of anesthesia.

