### Conclusions

STIM-MOTANA will provide the first protocol study to investigate MNS cerebral motor effect during general anesthesia for the detection of intraoperative awareness. Based on strong practical and theoretical scientific reasoning from our previous studies, an innovative MNS-based BCI used in this study would provide a way to detect intraoperative awareness during general anesthesia.

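### The secondary endpoint is written as movement-intention detection, but the trial records and scores only median nerve stimulation against rest

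*Protocol article*

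**What the plan says.** Under Secondary End Points, the protocol article states: "In this project, we need to reach the highest MI EEG detection accuracies as possible". The same sentence explains what this should achieve: "we need a very high true positive rate (ideally all AAGAs are detected) as well as a very low false positive rate (ideally no false" (the sentence ends with the word alarm). The section then names Riemannian-geometry classifiers as the means. It names no other outcome.

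The Statistics section describes a different task: "we will apply 4 different offline machine learning algorithms to detect the MNS at the cerebral level". It fixes the two classes: "The classification score will be computed for the MNS versus the rest class". Both windows are timed from the stimulus: the task window opens half a second after it, and the rest window opens 3 seconds ahead of it. The third objective in the Introduction agrees with this section, since it is to detect MNS under propofol in offline analysis.

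The Discussion (Principal Findings) says that the protocol proposes reliable, real-time detection of intraoperative awareness. It sets an accuracy above 90% as "the minimum required accuracy according to the clinical application". The Conclusions section adds that "an innovative MNS-based BCI used in this study would provide a way to detect intraoperative awareness during general anesthesia".

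**The concern.** The named endpoint and the planned score have different targets. One asks whether the patient intends to move, the other whether a stimulus has just been delivered. A true positive rate for MI needs windows in which MI is known to be present, and the article describes none.

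As written, two outcomes are possible. Either the secondary endpoint cannot be reported at all, or an MNS-versus-rest accuracy is placed under a heading that promises MI and AAGA detection. In the second case a reader could take a high figure as evidence that the device detects awareness. The trial would have shown only that the cortex still responds to the stimulus. For a safety application that difference decides what the trial may conclude.

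**Working it through.** The plan gives no figure for this endpoint, so there is none to reproduce. The check compares what the endpoint needs with what is recorded and scored, and then asks whether chance cases of AAGA could supply what is missing.

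**Step 1: what is recorded.**

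| Source in the protocol article | Content |
|---|---|
| Abstract, Methods; Primary End Points | Two occasions: awake before surgery and under general anesthesia |
| Study Design | Awake baseline is EEG during MNS without drug; MNS and EEG continue through the operation |
| Table 1 | EEG, electromyography and MNS; no MI task and no awareness assessment |
| Introduction | An MNS-with-MI condition is described, but for the earlier MOTANA trial |
| Study Duration | Participation ends with the end of surgery |

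Patient and Public Involvement mentions questionnaires at baseline and follow-up. It gives no content for them, and Table 1 schedules none. The Discussion says that AAGA is diagnosed only in retrospect. No label for awareness is therefore described.

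**Step 2: what each rate needs.**

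- MI true positive rate = MI windows flagged / all MI windows. No window is labelled MI, so the denominator is empty.
- MI false positive rate = windows without MI flagged as MI / all windows without MI. This needs a detector trained on MI. The planned detector is trained on MNS and should flag every post-stimulus window, whether or not the patient intends to move.
- MNS sensitivity = post-stimulus windows classified as MNS / all post-stimulus windows.
- MNS false positive rate = rest windows classified as MNS / all rest windows.

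Only the last two can be computed from the planned classes. They answer the third objective, not the endpoint as worded.

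**Step 3: could spontaneous AAGA supply the positive class?**

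Inputs: n = 30 (Study Population); p = 1% to 2% in high-risk practice (Abstract and Introduction). Applying this rate here is an assumption, because the eligibility criteria do not restrict the trial to high-risk surgery. A lower rate would give fewer cases.

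- Expected cases = n × p: 30 × 0.01 = 0.3; 30 × 0.02 = 0.6.
- Chance of no case = (1 − p)^30: 0.99^30 = 0.740; 0.98^30 = 0.545.
- Chance of at least one case: 1 − 0.740 = 0.260; 1 − 0.545 = 0.455.

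Suppose that one case occurred, was recognised and was detected. The exact two-sided 95% lower limit for the true positive rate would be 0.025^(1/1) = 2.5%. With two of two it would be 0.025^(1/2) = 15.8%. Neither says anything useful about a detector meant to catch nearly all cases.

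**The case against.** The best defence is that the operative text is consistent. The Abstract, the third objective and the Statistics section all say that the classifiers detect MNS, offline. On this reading the Secondary End Points paragraph gives motivation and then names a family of classifiers. Detecting MNS is also a sensible proof of concept: an MNS-based interface is of no use if propofol abolishes the response. Both points have weight. They show that the planned analysis is sound for its own question, and that the endpoint wording is what must change. They do not remove the problem, because the paragraph stands under an endpoint heading and MI detection is the only quantity it names.

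Several stronger readings are tempting, and the article does not support them.

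- **That the trial plans to infer awareness detection from its own data.** The conclusions are conditional and credit previous studies, and the Introduction calls the awareness interface a long-term goal. This is over-reach in wording, not a planned inference. The real-time and reliability claims, and the phrase that places the interface in this study, still attach it to this trial.
- **That the 90% requirement contradicts the wish for no false alarms.** One is a minimum and the other an ideal, so both can stand.
- **That the MNS score points the wrong way.** The Introduction says that "when a hand MI coincides with median nerve stimulation (MNS), the ERD/ERS is considerably reduced", and the Discussion concedes that deep anesthesia may abolish the response. A reader might infer that attempted movement and deep anesthesia look alike. Nothing in the article shows this. The Introduction's sentence goes on to say that MI is then easier to detect, and covariance-based classifiers use more than ERD amplitude.
- **That predictive values or alarms per hour can be worked out.** The article gives no alarm rule, no stimulus interval, and no separate sensitivity and specificity. Such figures would describe a hypothetical device.

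**Conclusion.** The point holds. The secondary endpoint as worded has no positive class and cannot be produced from the recordings described. The planned MNS-versus-rest score is a valid answer to the third objective and to nothing beyond it. Chance cases do not rescue the endpoint: 0.3 to 0.6 are expected among 30 patients, and none at all is the likelier outcome (74% to 55%).

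This rests on two assumptions. The first is that the article lists the recording conditions completely. The full protocol is not shown, but the article itself fixes the two classes as MNS and rest, so the mismatch does not turn on a detail left elsewhere. The second is that the high-risk AAGA rate applies to these patients; a lower rate strengthens the conclusion.

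The consequence is confined to the secondary endpoint and to the claims about awareness. ERD amplitude as the primary endpoint, its paired comparison and the number of patients are not touched.

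**What to change.** 1. In Secondary End Points, replace MI detection accuracy with MNS-versus-rest classification performance: sensitivity and false positive rate for MNS, reported for the awake recording and for each propofol concentration. Remove the definition of true positives as detected AAGAs.
2. In the Abstract (Conclusions), Principal Findings and Conclusions, limit what this trial can show to whether the cortical response to MNS is detectable under propofol.
3. Present detection of MI or awareness only as the long-term goal stated in the Introduction. This includes the real-time and reliability wording and the accuracy requirement above 90%.

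The cost is wording, recorded as a dated amendment, preferably before any classifier results are seen. It needs no new recordings, no further patients and no change to the planned classifiers, so it can be made although recruitment has begun. Adding an MNS-with-MI block to the awake session would be a separate design choice. It is not needed to correct this point, and patients already recorded would lack it.
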